**Prospective study of preoperative full MRI evaluation vs. standard preoperative evaluation in patient with rectal cancer**

**Study goals and objective**

To investigate the quality of preoperative evaluation in patients with rectal cancer, either as a full MR imaging (MRI) with MR rectum + MR colonography + MR liver and chest CT versus current standard preoperative evaluation (MR  rectum + endoscopy + abdominal /chest CT). Furthermore, to assess the economic aspects of full preoperative MRI evaluation vs. standard preoperative evaluation in patients with rectal cancer.

**Background**

Colorectal cancer (CRC) is among the most common cancer forms in Denmark with an approximate of 4300 new cases in Denmark annually, of which rectal cancer represents approximately 1400 new cases each year [1]. It is also well known that synchronous cancer and polyps are present in up to 11% and 58% in patients with CRC [2, 3, 4, 5, 6bv]. It is assumed that adenomas constitute a precursor for cancer [7] and it is thus speculated that the detection and removal of adenomas could reduce the incidence and mortality of colorectal cancer. Danish Colorectal Cancer Group (DCCG) and the Danish Surgical Society (DKS) currently recommend full colonic investigation as part of the preoperative evaluation, which also includes MRI of the rectum, ultrasound of the liver and chest X-ray (or abdominal /chest CT) to locate possible metastasis or synchronous tumors [8]. However, it is often difficult to implement the preoperative colonic investigation due to lack of capacity or tumor stenosis. A recent Danish study showed that up to 78% of all patients with colorectal cancer had not received the full colonic investigation preoperatively [9]. In this instance, the recommendation from DCCG & DKS is that patients, in the absence of complete colonic investigation preoperatively, should undergo colonoscopy within three months postoperatively.

Within the last 15 years new non-invasive imaging techniques have been developed, this includes MR colonography (MRC). Like conventional colonoscopy, ​​MRC requires bowel cleansing, since feces can create artifacts that can hide or mimic polyps and abnormalities. After colonic cleansing the colon is distended by water using a rectal catheter. Since it is only water that needs to pass through a possibly stenotic colon segment, there is a better chance to successfully examine the entire colon compared to a colonoscopy. A recent study showed a 98% success rate using MRC to examine the entire colon in patients with CRC having colon stenosis [10]. The MRC is preformed after the colon is fully distended with water and the scan times are between 10 and 15 minutes. Data processing, reconstruction and analysis are made at an independent workstation.

The advantages of MRC are its non-invasive nature, short examination time, and the fact that sedation is unnecessary. This makes it possible for patients to be discharged directly after the imaging procedure as opposed to the necessity for admission after a colonoscopy until the effects of the sedative drugs have worn off. Furthermore, it is assumed that patient compliance is much higher in MRC, since the majority of the patients find it less unpleasant than colonoscopy [11, 12].
MRI of the liver is a well-known procedure that has shown good results in the diagnosis of hepatic metastases and primary cancers. Several studies have shown that it is equal or better than CT and ultrasound of the liver [13, 14].

Currently there are no studies, which make the overall preoperative assessment by means of one investigating technique, namely MRI. We have previously studied the sensitivity/specificity and patient satisfaction by MRC with fecal tagging [15]. In this study we want to investigate the quality of MRC with bowel cleansing, also assessing the economic aspects of an overall examination of the rectum, colon and liver in patients with rectal cancer.

**Design**

Prospective randomized clinical trial. Patients diagnosed with rectal cancer are invited to participate in a full preoperative MRI investigation (rectum, liver ad colonography) + chest CT or to participate in the standard preoperative evaluation (rectal MRI, +/- endoscopy and abdominal/thoracic CT) to exclude metastasis. The randomization is computerized.

The studies are evaluated by two blinded investigators. All patients will also receive an intraoperative ultrasound of the liver, which will serve as the gold standard for liver examination.

**Study population:**

140 patients with histopathological confirmed rectal cancer, scheduled for surgery.

**Inclusion criteria:**

Patients with rectal cancer scheduled for surgery.

**Exclusion criteria:**

Missing informed consent

IBD (Inflammatory bowel disease)

Pacemaker

Metal parts in the body

Claustrophobia

Psychiatric disorders

Age under 18

Pregnancy

Kidney diseases

Heart disorders (i.e. arrhythmia)

**Methods:**

Patients scheduled for surgery after histology confirmed rectal cancer are invited to participate in the study after obtaining an informed consent. After acceptance patients are randomized by a computer generated randomization code, to either receive the full preoperative MRI evaluation (rectum, liver ad colonography) + chest CT or to participate in the standard preoperative evaluation. The patients are randomized in blocks of groups of 10 patients. Both groups will also receive an intraoperative ultrasound of the liver, which will serve as the gold standard for liver examination.  After the first 140 patients are included in the study, additional participants will be included in blocks of 10 if patients have dropped out of the study. This will ensure that the overall enrolled number of patients who have completed the project will be at a minimum of 140.

The day before the full MRI investigation, patients have to carry out a colonic cleansing, following the guidelines of bowel cleansing with Moviprep®.

The patients not included in the study will receive the standard preoperative evaluation.

During the procedure the patient is placed in supine position, where a rectum scan will be performed followed by a liver scan. Hereafter, the colon will be distended with water by a rectal catheter and the remaining scans will be conducted. Each of the MRC scan sequences are about 20 sec. with patient breath hold during each sequence. MRI contrast agent is administered to emphasize pathology in the T1 MR imaging.

Furthermore, patient will be administered intravenously Buscopan®, to reduce bowel movement and thus imaging artifacts.

Data processing, reconstruction and analysis are made at an independent workstation.

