**Patient recruitment:**

Patients will be recruited in *Gastroenheden*, surgical gastroenterology section, Herlev University Hospital, as a part of their first outpatient visit after having the cancer diagnosis confirmed. The patient will be contacted directly by research year student [name] or another member of the research group.

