**Statistics:**

Sample size is calculated to be 50 patients in a group to ensure at least 1 synchronous cancer in each group with a 95% likelihood, assuming that the prevalence of synchronous cancer is 6%. To further strengthen the study the number is increased to 75 patients in each group.

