**Logistical framework:**

The project will be performed at the Department of Radiology and Gastroenheden, Herlev University Hospital.

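### A single fixed block size of 10, printed in the protocol of a one-hospital trial whose own research group recruits, makes part of the allocation sequence foreseeable; varied and undisclosed sizes would nearly remove this

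*Protocol*

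**What the plan says.** All references are to the protocol; no SAP is shown.

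- **Block size.** Methods: "The patients are randomized in blocks of groups of 10 patients". For replacements after the first 140, Methods adds that "additional participants will be included in blocks of 10 if patients have dropped out of the study". No second or varying size and no stratification factor is mentioned.
- **Order of events.** Methods: "After acceptance patients are randomized by a computer generated randomization code". Allocation therefore follows consent.
- **Who recruits.** Patient recruitment names a research year student "or another member of the research group".
- **Where.** Logistical framework: "The project will be performed at the Department of Radiology and Gastroenheden, Herlev University Hospital". There is one hospital, so the natural reading is one sequence.
- **Blinding.** Design: "The studies are evaluated by two blinded investigators". Nobody else is described as blinded. According to Methods, the MRI arm involves bowel cleansing the day before and filling the colon with water, so staff can see which arm a patient was in.
- **Numbers.** Study population: "140 patients with histopathological confirmed rectal cancer, scheduled for surgery". Statistics: "the number is increased to 75 patients in each group". No allocation ratio is stated in words; 1:1 is inferred from the equal groups.

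**The concern.** In a block of fixed size, the remaining places are determined once one arm has used its quota. Anyone who knows the block size and the allocations so far can see when that happens. Here the size is in the protocol, blocks would end at patients 10, 20, 30 and so on, and the recruiting group sees the arms as they are given.

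Foreknowledge of the next arm matters because recruiters decide whom to invite. Several exclusion criteria (claustrophobia, psychiatric, kidney and heart disorders) carry no threshold, and some bear on whether a patient tolerates MRI. A patient who is not included simply receives the standard evaluation, so passing someone over leaves little trace. The Background names tumour stenosis as an obstacle to full colonic examination. Selection on stenosis or expected tolerance, even if unintended, would make the arms differ in features tied to completeness, detection and cost.

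The comparison rests on few events. At the 6% prevalence of synchronous cancer assumed under Statistics, an arm of 70 would contain about 0.06 × 70 = 4.2 cases.

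**Working it through.** The protocol gives no figure for predictability, so there is none to reproduce.

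**Inputs**
- Block size 10 (Methods).
- Total 140 (Study population, Methods), which is 14 blocks. The Statistics section implies 2 × 75 = 150, which is 15 blocks. That mismatch is a separate matter; both totals are shown where it makes a difference.
- Five places per arm in each block, m = 5 (inferred from equal groups).
- A recruiter who knows the block size, where blocks begin and all past allocations (assumption; the protocol does not say so).

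**1. Allocations that are certain in advance**

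A place is certain when one arm's five places are already used. The expected number per block is 2m/(m + 1) = 10/6 = 1.67, or 16.7% of 10. Enumerating all C(10,5) = 252 possible blocks gives the same value.
- For 140: 14 × 1.67 = 23.3 patients.
- For 150: 15 × 1.67 = 25 patients.

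**2. What is guaranteed and what is average**

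Only the last place is certain in every block, so the minimum is 14 of 140. The last two places hold different arms with probability 5/9, so in 56% of blocks exactly one place is known in advance. The figure of 23 is an average.

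**3. Best guess**

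A recruiter who always guesses the arm with more places left is right, on average, m + (4^m / C(2m, m) − 1)/2 times per block:

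5 + (1024/252 − 1)/2 = 5 + 1.53 = 6.53 of 10, or 65.3% (about 91 of 140), against 50% under simple randomisation.

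**4. Effect of varied sizes**

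These are simulations with N = 140 and sizes drawn with equal probability. The recruiter knows the set of sizes and all past allocations, but not the order of the sizes. The sets are illustrations and do not come from the protocol.

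| Block sizes | Certain allocations | Of 140 | Best guess right |
|---|---|---|---|
| 10 only (protocol) | 16.7% | about 23 | 65% |
| 8, 10, 12 | about 1.3% | about 2 | 65% |
| 6, 8, 10, 12 | about 0.8% | about 1 | 66% |
| 4, 6, 8 | about 2.4% | about 3 | 68% |

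Varying the size removes nearly all certain knowledge. It does not lower the best-guess rate, and small blocks raise it. If the size is known, the rate is 70.8% for blocks of 4, 68.3% for 6 and 66.6% for 8.

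**The case against.** Permuted blocks of fixed size are a valid and common method, ten is a fairly large block, and nothing in the protocol is contradicted or miscalculated here. Four further arguments deserve weight.

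- **Consent comes first.** Methods already places randomisation after acceptance, so a patient cannot be refused once the arm is known. This stands and limits the risk. It does not remove it, because the invitation comes before consent and recruiters choose whom to invite.
- **The point of approach is fixed.** Recruitment is tied to the first clinic visit once the diagnosis is established, and patients are awaiting surgery. That leaves little room to hold someone back until the other arm comes up. This stands for deferral; it does not prevent selective invitation.
- **Evaluators are blinded.** This bears on how images are read. It does not hide earlier allocations from those who recruit.
- **The figures assume an ideally informed recruiter.** This stands. If the recruiter does not know every earlier allocation, or the previous one is not yet known when the next patient is approached, less can be foreseen.

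A reader might also infer that concealment is absent because no independent holder of the list is named. The protocol does not support that: such details are often kept in other documents, and their absence here shows nothing either way.

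**Conclusion.** The point holds as a modest design weakness. The single published block size makes the last place of each block (14 of 140) certain, and on average 16.7% of allocations (about 23 of 140, or 25 of 150), for a recruiter who knows past allocations and block boundaries. It rests on three inferences: 1:1 allocation within blocks, one unstratified sequence, and arms that staff can see once given. The awkward wording about blocks of groups is read as a block size of 10, which the replacement rule supports.

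Three stronger readings are not supported.
- It cannot be said that several late places of every block are always known; only the last one is.
- It cannot be said that about 23 patients would be steered, or that the results would be biased by any given amount. The figures are an upper bound on predictability, and the protocol offers nothing from which to estimate bias.
- The 65% best-guess rate cannot be counted as a harm that varied block sizes would cure, because it stays about the same.

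**What to change.** In Methods, for both the main and the top-up patients, replace the single block size with sizes varied at random that are on average no smaller than now, for example 8, 10 and 12. State in the protocol only that block sizes vary, and keep the sizes themselves out of the version that recruiters hold. Keep the present order of consent before randomisation.

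Certain allocations then fall to about 1% (1 to 2 of 140) even if the set of sizes becomes known. Sizes 4, 6 and 8 should not be used, because they raise the best-guess rate to about 68%.

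The cost is regenerating a computer list, with no extra patients or procedures. The final block may be incomplete, so arm totals may differ by a few patients: at most 6 with a largest block of 12, against 0 with 14 complete blocks of 10.

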**Safety Considerations:**

Department guidelines are followed. Monitoring for MRI scanning with contrast is performed by radiology technicians and there will be an immediate access to a radiologist in necessary cases.

**Patient recruitment:**

Patients will be recruited in *Gastroenheden*, surgical gastroenterology section, Herlev University Hospital, as a part of their first outpatient visit after having the cancer diagnosis confirmed. The patient will be contacted directly by research year student [name] or another member of the research group.

**Informed consent:**

All potential study participants will receive oral and written information about the study. Inclusion takes place after obtaining informed consent.

**Risks and side effects:**

The MRI contrast agent (Gadolinium) is used in daily routine MRI scans and is administered intravenously. Side effects are extremely rare and may present as warmth, a metallic taste in the mouth, palpitations, headaches and dizziness associated with the injection and in rare cases hives and nausea.

Buscopan® is also a common agent used in clinical routine practice such as endoscopy with rare side effects. Known side effects are dry mouth, pupil dilation, mucosal dryness, heart palpitations and urinary retention.

Moviprep® is a routine bowel cleansing agent with extremely rare side effects. These includes bloating, nausea; rectal irritation; stomach cramps or pain, vomiting, muscle pain, shivering, diarrhea and dizziness.

There is a possibility of scanner induced loud noises during MRI scanning. Patients will be offered a hearing protection device.

There is always a radiologist in the immediate vicinity during the MRI scans. The scans will take place at the Radiology department at Herlev University Hospital.

**Ethical aspects:**

A full preoperative MRI evaluation has potentially enormous consequences for investigation and diagnosis in patients with colorectal cancer. There are many expected advantages compared to the existing diagnostic tools (as mentioned above) in this procedure if validated and developed.

This applies both to the patient but also on a socioeconomic perspective. During the study, project subjects will receive a more extensive diagnostic investigation.

The expected beneficial effects of the project, both for the individual patient and for future patients, thereby justify the studies predictable risks, side effects and disadvantages.

**Statistics:**

Sample size is calculated to be 50 patients in a group to ensure at least 1 synchronous cancer in each group with a 95% likelihood, assuming that the prevalence of synchronous cancer is 6%. To further strengthen the study the number is increased to 75 patients in each group.

**Logistical framework:**

The project will be performed at the Department of Radiology and Gastroenheden, Herlev University Hospital.

**Approval:**

The project has been approved by the Regional Ethics Committee and the Danish Data Protection Agency.

**Time frame:**

The project is intended to have a time span of 48 month.

